### Data collection, management, and statistical analysis

Clinical and anthropometric data including a history of disease, time to surgery, current medication, staged or single-step surgery, comorbidities, and the results of routine assessments (clinical chemistry, imaging) at baseline will be gathered by chart review and interview. Furthermore, postoperative complications (wound healing problems, non-union, infections) are recorded in both treatment groups. At the time of enrollment, patients will receive a unique identification code (ID), and all documents and hard copies generated for the purpose of this trial will be linked to this identifier. The underlying key will be stored in a password-protected file accessible only to the principal investigators ([name], TM). Of note, the evaluator will be unblinded only after the last patient has finalized the study examinations. Regardless of this, access to the data will be limited to the researchers involved in this trial.

Data will be analyzed using the SPSS statistical package 26.0 (SPSS Inc., Chicago, IL) and Sigma Plot V10 (Systat Software GmbH, Erkrath, Germany) for graphical presentation. The normal distribution of continuous variables will be evaluated by the Kolmogorov-Smirnov test, descriptive summary measures will be calculated. Categorical variables are summarized as numbers and percentages. For comparison of the categorical variables, the chi-square test or Fisher’s exact test will be used, as appropriate. Repeated measure analysis will allow for longitudinal examination of the treatment effects and differences between the study groups. Data from all randomized participants will be included (intent-to-treat analysis). No missing data imputation will be performed, and in view of the rather small number of participants per treatment arm, neither subgroup or adjusted analyses are planned. During the study, patients and personnel are encouraged to mention all problems related to the study investigations and especially to the acceptance of the contact-less 3D optical scanning procedure. At the time of discharge, patients randomized to RICE^+^ will be asked by the one in charge for the application of the device-based negative pressure therapy to rate this additional treatment on a scale ranging from 1 (very good) to 5 (no effect). Proceeding to the main trial will be deemed feasible if (a) at least two-thirds of the patients allocated to RICE^+^ will retrospectively judge this additional treatment positive and (b) at least two-thirds of all patients accept the repetitive contact-less 3D optical scanning procedure.

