## Methods/design

### Aim of the study

This monocentric, evaluator-blinded randomized controlled pilot-trial aims (i) to obtain an estimate on the standard deviation of the normalized ankle volume during postoperative recovery and (ii) to assess the feasibility of the proposed randomized allocation to the treatments and the suggested outcome measures. The latter include the demand for analgesics, the perception of pain, the rate of complications, the mobility of the joint, walking abilities, and skeletal calcium accrual together with bone mineral density. In summary, the results may broaden the knowledge on the interference between soft tissue swelling, functional outcome, and bone metabolism.

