### Design and setting of the study

This is a single-center evaluator-blinded randomized controlled pilot trial with two parallel groups and a 1:1 allocation ratio of patients receiving surgical fixation of an unilateral ankle fracture. The study is going to be conducted at the Department of Traumatology, Hand and Reconstructive Surgery at Rostock University Medical Center. Starting from the 2nd postoperative day, there will be daily interventions for up to 10 days (i.e., the time of hospitalization). Repeated measures of outcome will be performed at baseline (prior to surgery), during the intervention period, and during the 12-week follow-up period. The study will be performed according to the ethical standards of the Institutional Ethics Committee (approval number: A 2020-0092) and in accordance with the Declaration of Helsinki.

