### Outcome measures

All measures will be taken at baseline and at pre-specified time points during the treatment and follow-up period (Fig. 1 and Table 2). Non-contact 3D scanning will be used to quantify postoperative swelling relative to the healthy/unaffected ankle by an evaluator blinded for the treatment. Scanning will start on the evening of the 2nd postoperative day. Subsequent measurements will be taken every 24 h until discharge from the hospital and by the same blinded evaluator. This data will allow to determine the variability of the normalized ankle volume and the kinetic of edema reduction (primary outcome). Secondary outcome measurements consist of the daily recordings of the individual pain perception by means of numeric analog scale, of the type and amount of analgesics, the quantification of the range of motion at both ankles (dorsi- and plantarflexion) with a goniometer at the time of discharge from the hospital and during follow-up visits. Walking abilities (factors of imbalance, ground reaction force) at the time of discharge from the hospital and during the follow-up period will highlight the functional outcome. Bone mineral density will be determined by means of quantitative pulse echography (Bindex®, Bone Index Finland Ltd., Kuopio, Finland) [24] at the time points indicated (Table 2). Sampling of blood and urine is on a voluntary base only, and these samples will be used to investigate the ratio of naturally occurring stable calcium isotopes (δ^44/42^Ca) in the serum and urine as a marker of bone mineral balance during fracture healing.

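### The daily primary scans stop at each patient's own discharge, but no reference day is fixed for the planning SD or the arm comparison, and the analysis wording does not settle how series of unequal length are handled

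*Protocol article*

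**What the plan says.** All references are to the protocol article.

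- **Aim of the study:** the first aim is "to obtain an estimate on the standard deviation of the normalized ankle volume during postoperative recovery". No day is named.
- **Outcome measures:** scanning starts on the evening of postoperative day 2. "Subsequent measurements will be taken every 24 h until discharge from the hospital and by the same blinded evaluator". Then: "This data will allow to determine the variability of the normalized ankle volume and the kinetic of edema reduction (primary outcome".
- **Design and setting of the study:** "there will be daily interventions for up to 10 days (i.e., the time of hospitalization". Length of stay therefore differs between patients.
- **Table 2:** ankle swelling is also scheduled for the day before surgery, at discharge and at weeks 2, 4, 6 and 12. The subsection on the primary objective, however, is confined by its heading to recovery in hospital.
- **Data collection, management, and statistical analysis:** "Repeated measure analysis will allow for longitudinal examination of the treatment effects and differences between the study groups". The next sentences read "Data from all randomized participants will be included (intent-to-treat analysis). No missing data imputation will be performed", and subgroup and adjusted analyses are ruled out.

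The article gives no discharge criterion, no distribution of length of stay and no expected SD or effect.

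**The concern.** The number of daily scans a patient contributes is that patient's length of stay. Stay is determined after randomisation, and it may plausibly depend on swelling and, through swelling, on treatment. The set of patients with a scan therefore shrinks from day to day and may become selected.

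An SD of normalised ankle volume during recovery is then not one quantity. On day 2 it describes nearly everyone; on day 7 it describes those not yet discharged. The same holds for a difference between arms. Without a stated day, the choice can be made after the data are seen.

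The analysis paragraph leaves open which method is meant, and the methods differ sharply for series of unequal length. Complete-case repeated-measures ANOVA without imputation drops every patient who lacks a day, contrary to the promise that "Data from all randomized participants will be included (intent-to-treat analysis". The SD is the pilot's main numerical product for a later, adequately powered trial, so an imprecise or too small value would be carried forward.

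**Working it through.** **1. The plan's own figure.** The only sample-size figure is 25 per arm, and 2 × 25 = 50 agrees with the stated total. There is no alpha, power, effect or SD, so there is no power calculation to reproduce.

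**2. Precision of an SD as patients leave.** The 95% limits are the estimate times √[(n−1)/χ²(0.975; n−1)] and √[(n−1)/χ²(0.025; n−1)].

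| n | lower multiplier | upper multiplier |
|---|---|---|
| 50 | 0.84 | 1.25 |
| 25 | 0.78 | 1.39 |
| 10 | 0.69 | 1.83 |
| 5 | 0.60 | 2.87 |

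This loss occurs whatever the reason for discharge.

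**3. Illustrative simulation.** Every input is an assumption, because the article supplies none.

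- Normalised volume (healthy side = 100) averages 120 on day 2 and falls 1.5 points a day. RICE+ falls a further 0 or 0.5 points a day.
- Between-patient SD is 6 and within-patient SD is 2, so the total SD is √(36 + 4) = 6.3.
- Scans run on days 2–10. From day 3 the logit of daily discharge is −1.3 − k × (last volume − 116)/6. Here k = 0 means unrelated to swelling, k = 1 moderate and k = 2 strong dependence.

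Check for k = 0: daily discharge probability is 1/(1 + e^1.3) = 0.214, so 25 × 0.786^5 = 7.5 per arm remain on day 7 and 25 × 0.786^8 = 3.6 on day 10. Both match the simulation.

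Day 7, extra RICE+ decline of 0.5 a day (true difference 5 × 0.5 = 2.5 points):

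| k | remaining of 25, RICE / RICE+ | difference: true → patients still in hospital | SD: true → patients still in hospital | difference, complete cases | mixed model: difference; SD |
|---|---|---|---|---|---|
| 0 | 7.5 / 7.5 | −2.52 → −2.58 | 6.33 → 6.31 | −2.40 | −2.42; 6.33 |
| 1 | 8.9 / 7.7 | −2.49 → −2.09 | 6.34 → 5.26 | −1.43 | −2.56; 6.23 |
| 2 | 9.6 / 7.7 | −2.55 → −1.77 | 6.34 → 4.65 | −0.29 | −2.52; 6.37 |

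- SD shortfall: 1 − 5.26/6.34 = 17% (k = 1); 1 − 4.65/6.34 = 27% (k = 2).
- Attenuation of the difference: 1 − 2.09/2.49 = 16%; 1 − 1.77/2.55 = 31%.
- No true effect: the difference among those remaining stays at about 0 for every k, but the SD still falls from 6.33 to 5.27 (k = 1) or 4.68 (k = 2).
- Complete series: 12–16% of patients have every scan on days 2–10, that is 6–8 of 50.

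The still-in-hospital columns rest on 100,000 simulated patients per arm. The complete-case and mixed-model columns come from single runs of 3,000 per arm. About 0.13 × 3,000 = 390 complete cases per arm give a standard error near 6.3 × √(2/390) = 0.45, so the complete-case column shows direction and rough size only. The mixed model used no imputation. It recovers the true values because discharge was made to depend only on measured swelling and because the fitted form matches the simulated one.

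**The case against.** The strongest reply is that the article never names ANOVA, listwise deletion or day-by-day summaries. A likelihood mixed model uses all observed scans of all randomised patients, imputes nothing and is available in the SPSS version named. Under that reading the statements are compatible. This stands: not imputing is not the fault, and there is a conflict only under the complete-case reading.

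A second reply is that the type of model and the contrast day belong in a statistical analysis plan, which may exist. This stands in part. The article need not give a covariance structure. But the day to which the SD refers is part of what the primary quantity is, and the article itself commits to an analysis set and a missing-data rule without saying how they work with series that end at discharge.

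Third, Table 2 provides scans scheduled for every patient regardless of stay, and the day-2 scan is a common early point. That is correct, and the fix uses it. It does not remove the problem: the primary subsection is confined to the hospital stay, and by the evening of day 2 only one device session has taken place.

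Fourth, the two progression criteria concern patients' judgement of the device and acceptance of scanning. Neither uses the SD or the arm difference, so the feasibility decision is untouched. This also stands.

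A reader might go further and infer that the effect and the SD are biased. The documents do not support that. Bias needs discharge linked to swelling and a per-day or complete-case method, and the article states neither.

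A reader might also infer that the main trial would come out much too small. Squaring the SD ratio alone gives (5.26/6.34)² = 0.69 and (4.65/6.34)² = 0.54. But if the difference comes from the same patients, N changes by [(5.26/2.09)/(6.34/2.49)]² = 0.98 or [(4.65/1.77)/(6.34/2.55)]² = 1.12. Even the direction is open, so no sample-size error can be claimed.

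**Conclusion.** The point holds in a conditional form. It is certain from the text that the daily series ends at a patient-specific event after randomisation, that no reference day is set for the SD or the arm comparison, and that the analysis wording permits methods with very different consequences.

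The rest depends on what is done:

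- Complete-case repeated-measures ANOVA would drop patients with shorter stays and break the stated intent-to-treat rule.
- Day-by-day SDs lose precision in any case.
- If less swollen patients leave earlier, those SDs are about 17–27% too small, and a true arm difference is attenuated by about 16–31%, under the assumed inputs.
- If discharge is unrelated to swelling, there is no bias.
- If there is no true effect and both arms follow the same discharge rule, only the SD is affected.

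The percentages are illustrations, not predictions. This is a worthwhile and cheap improvement to the pilot's first aim; it does not invalidate the pilot.

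**What to change.** Before unblinding, add wording to this effect:

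- Normalised ankle volume is analysed with a likelihood-based linear mixed model (SPSS MIXED) on every observed scan of every randomised patient. Terms are arm, postoperative day (categorical or otherwise flexible, not forced to be linear) and arm-by-day.
- The planning SD and the primary contrast are taken at one pre-stated early postoperative day on which most patients are expected still to be inpatients. They are supported by the week-2 scan that Table 2 schedules for all patients. The documents do not determine the day; the sponsor should choose it from its own length-of-stay experience.
- The number scanned per arm and day, and length of stay by arm, are reported.
- A sensitivity analysis examines discharge that depends on outcome.

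If preoperative normalised volume is added as a covariate, the sentence ruling out adjusted analyses must be amended.

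The cost is wording and somewhat more analysis work; no visit or scan is added. Two limits should be stated. Model-based values for discharged patients assume that scans are missing at random given the observed data. They also describe patients for whom the inpatient treatment has already stopped, so they should not be read as the course under continued treatment.

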**Methods and analysis:**

This is a single-center, evaluator-blinded randomized pilot trial to investigate postoperative swelling in adults requiring surgical fixation of a closed unilateral ankle fracture. A total of 50 patients will be recruited and randomly assigned to RICE or RICE^+^ prior to surgery. All patients will undergo evaluator-blinded measurements of the ankle volume the day before surgery and subsequently from the evening of the 2nd postoperative day every 24 h until discharge. RICE will be initiated right after surgery and continued until discharge from the hospital in all patients. Additional application of negative pressure therapy (RICE^+^) will be initiated on the morning of the 2nd postoperative day and repeated every 24 h until the time of discharge from the hospital. Outcome measures are (i) the relative amount and the time course of the postoperative swelling, (ii) the demand for analgesic therapy (type and amount) together with the perception of pain, (iii) the rate of complications, and (iv) mobility of the ankle joint and the recovery of walking abilities during a 12-weeks follow-up period. Serum and urine samples taken prior to sugery and during postoperative recovery will allow to evaluate the ratio of naturally occurring stable calcium isotopes (δ^44/42^Ca) as a marker of skeletal calcium accrual.

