#### Monitoring of the ankle volume during postoperative recovery in the hospital

The primary objective of the study is to investigate the amount of postoperative swelling relative to the application of RICE or RICE^+^. To ensure objective evaluation, a contact-less 3D optical scanning procedure (Artec®eva, Artec Studio, Luxembourg, Luxembourg) will be used to determine the volume of both ankles. To account for the interindividual variability of the ankle volume, per patient, the volume of the fractured ankle will be normalized to the one determined at the healthy site. The scan will cover an area ranging from the planta pedis up to one-third of the lower leg. The latter is defined as the distance between the medial knee joint space and the medial ankle. The upper border of the area to be scanned will be marked with permanent felt-tip pens. Proprietary software of the scanner (Artec studio V15, Artec3D, Luxembourg, Luxembourg) will be used to quantify ankle volumes. To minimize the effects of wound dressing, in all patients, a sterile and transparent film dressing (OPSITE® Post-OP visible, Smith & Nephew Woundcare, Hamburg, Germany) will be applied on the 2nd postoperative day .

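### Small arms are no reason to leave out the one baseline value of the outcome: the pre-operative ankle volume can be a covariate at almost no cost, and the residual SD and correlation would help to size the main trial

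*Protocol article*

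**What the plan says.** The section on data collection, management and statistical analysis gives its reason, "in view of the rather small number of participants per treatment arm", and concludes that "neither subgroup or adjusted analyses are planned". It makes no exception for the baseline value of the outcome. The longitudinal analysis is described in one sentence: "Repeated measure analysis will allow for longitudinal examination of the treatment effects and differences between the study groups". Whether the pre-operative scan enters as a response, as a covariate or not at all is not stated.

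The baseline measurement itself is planned. The abstract says "All patients will undergo evaluator-blinded measurements of the ankle volume the day before surgery". The outcome section says "All measures will be taken at baseline and at pre-specified time points during the treatment and follow-up period". Table 2 marks ankle swelling, analgesic demand and pain at the visit before surgery, and the design section lists baseline among the times of repeated measurement. The sentence "Scanning will start on the evening of the 2nd postoperative day" reads as the start of the postoperative series and does not cancel the earlier scan.

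The first aim is "to obtain an estimate on the standard deviation of the normalized ankle volume during postoperative recovery". The outcome is a within-patient ratio: "the volume of the fractured ankle will be normalized to the one determined at the healthy site". The discussion says the results will inform a decision on an adequately powered multicenter trial.

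**The concern.** Excluding adjustment because the arms are small joins two different matters. Subgroups and long covariate lists are unwise with 25 patients per arm. One pre-specified baseline value of the outcome is different: it costs very little, and chance baseline imbalance is larger in small arms than in large ones.

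Dividing by the healthy ankle removes differences in ankle size but not differences in pre-operative swelling. That swelling may vary considerably, since any closed unilateral fracture type scheduled for surgery is eligible, and time to surgery and staged surgery vary enough to be recorded.

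Two things are at stake. One is the precision of the comparison of swelling between arms, which the section on monitoring of ankle volume names as the primary objective. The other is the set of planning figures for the main trial. A baseline-adjusted main trial is sized on the residual SD, or on the raw SD with the baseline-outcome correlation. Only the raw SD is planned.

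**Working it through.** **Inputs from the article.** 25 per arm, 50 in total, 1:1 allocation. The size is taken from recommendations for feasibility studies. No alpha, power, effect size, SD or correlation is given, so the only check on the stated figure is 2 × 25 = 50, which agrees.

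**Assumptions.** Baseline-outcome correlation ρ = 0.3, 0.5 or 0.7. Illustrative main-trial settings: two-sided alpha 0.05, 80% power, effect 0.5 raw SDs. One follow-up value, with equal variances before and after surgery, unless stated otherwise.

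**Cost of one covariate.** A two-arm comparison of 50 patients has 50 − 2 = 48 residual degrees of freedom, and the covariate uses one. The finite-sample variance penalty is 1 + 1/(50 − 4) = 1.022, about 2% if ρ = 0. Break-even is where (1 − ρ²) × 1.022 = 1, so ρ = √(1/47) = 0.146.

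**Gain.** The variance factor with adjustment is 1 − ρ². The penalized factor multiplies this by 1.022. For comparison, the factor for a change-from-baseline contrast is 2(1 − ρ).

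| ρ | Adjusted | Adjusted, with penalty | SD factor | Change from baseline |
|---|---|---|---|---|
| 0.3 | 0.91 | 0.93 | 0.954 | 1.4 |
| 0.5 | 0.75 | 0.77 | 0.866 | 1.0 |
| 0.7 | 0.51 | 0.52 | 0.714 | 0.6 |

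The variance reduction is therefore 9%, 25% or 49% before the penalty, and 7%, 23% or 48% after it. A change contrast is less precise than adjustment in every row. At ρ = 0.3 it is less precise than ignoring the baseline.

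**In this pilot.** The smallest difference detectable with 80% power is (1.96 + 0.84) × √(2/25) = 0.79 SD unadjusted. Multiplied by the SD factor it becomes 0.76, 0.69 or 0.57 SD.

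**Chance imbalance.** The baseline difference between two arms of 25 has an SD of √(2/25) = 0.28 baseline SDs. If the baseline is left out of the model and ρ = 0.5, an imbalance of that size shifts the contrast by 0.5 × 0.28 = 0.14 SD.

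**Several postoperative scans.** For the mean of k values with all correlations equal to ρ, the unadjusted variance is v = (1 + (k − 1)ρ)/k and the adjusted variance is v − ρ². With k = 3 the ratio is 0.83, 0.63 or 0.39, so the gain does not vanish with daily scans. Equal correlations are a simplification, because surgery lies between the baseline scan and all the others.

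**Main trial.** Sizing an adjusted trial on the raw SD inflates it by 1/(1 − ρ²) = 1.10, 1.33 or 1.96. At an effect of 0.5 SD that means 63 per arm where 58, 48 or 33 would do.

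**The case against.** Several points on the other side are fair.

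- **A reader might infer that adjustment is forbidden.** The text says only that none is planned.
- **A reader might infer that baseline imbalance passes undiminished into the treatment contrast.** The design section counts baseline among the repeated measurements, so the scan may already enter the analysis as a time point, with the treatment effect read from the group-by-time term. The article does not settle this. If so, the imbalance is handled, but as a change-type contrast, which the table shows to be less precise. Only a model that holds the baseline mean equal in both arms would match covariate adjustment, and nothing in the text says that.
- **A reader might infer that the pilot yields the wrong SD.** The raw SD is exactly what the aims promise, and it is right for an unadjusted main trial. The article does not say how the main trial will be analysed. If that trial adjusts for baseline, the error makes it too large rather than underpowered.
- **The missing quantities are recoverable.** The residual SD and the correlation can be computed later from the data collected.
- **The correlation may be modest.** Surgery is a second injury with new swelling, and the introduction says that pre-operative edema has to be relieved before closure. At ρ = 0.3 the gain is worth about two patients per arm (25/0.91 = 27.5).
- **Progression is unaffected.** Both criteria concern patient acceptance, not the treatment contrast.

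These points limit the consequence. They do not rescue the stated reason, which is still wrong for a single baseline covariate, and the comparison of swelling remains a named objective.

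**Conclusion.** The point holds as a free improvement. Small arms justify excluding subgroups and multiple covariates, but not the single baseline value of the outcome. That covariate costs about 2% in variance at worst and pays for itself above a correlation of about 0.15. The gain of 9%, 25% or 49% rests on assumed correlations of 0.3, 0.5 and 0.7 and on a single follow-up value; its true size is unknown.

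Nothing here invalidates the pilot. The raw SD meets the stated aim but does not suffice to plan a baseline-adjusted main trial, and used alone it would make that trial larger than needed.

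**What to change.** In the statistical analysis section:

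1. Keep the exclusion of subgroup analyses and of other covariates.
2. State that the repeated-measures model for normalized ankle volume includes the pre-operative normalized ankle volume as a covariate, and that the model for pain includes the pain score from the day before surgery.
3. Report the raw SD, the residual SD and the baseline-outcome correlation, each with a confidence interval, for planning the main trial. The intervals matter: with 48 degrees of freedom the 95% limits for an SD run from 0.83 to 1.25 times the estimate.

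The cost is a few lines of text, one covariate per model and three reported quantities. No new measurements or patients are needed. Since no imputation is planned, a patient without a pre-operative scan would drop out of the adjusted model, so the number of such patients should be reported.
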